## Abstract

**Background:**

Upper limb dysfunction is common after stroke, posing an important challenge for post-stroke rehabilitation. The clinical efficacy of acupuncture for the recovery of post-stroke upper limb function has been previously demonstrated. Mirror therapy (MT) has also been found to be effective. However, the effects of acupuncture and MT have not been systematically compared. This trial aims to elucidate the synergistic effects of acupuncture and MT on upper limb dysfunction after stroke.

**Methods:**

A 2 × 2 factorial randomized controlled trial will be conducted at the rehabilitation hospitals affiliated with Fujian University of Traditional Chinese Medicine. A total of 136 eligible subjects will be randomly divided into acupuncture treatment (AT), MT, combined treatment, and control groups in a 1:1:1:1 ratio. All subjects will receive conventional treatment. The interventions will be performed 5 days per week for 4 weeks. AT, MT, and combined treatment will be performed for 30 min per day (combined treatment: AT 15 min + MT 15 min). The primary outcomes in this study will be the mean change in scores on both the FMA and WMFT from baseline to 4 weeks intervention and at 12 weeks follow-up between the two groups and within groups. The secondary outcomes are the mean change in the scores on the Visual Analogue Scale, Stroke Impact Scale, and modified Barthel index. Medical abstraction of adverse events will be assessed at each visit.

**Discussion:**

The results of this trial will demonstrate the synergistic effect of acupuncture and MT on upper limb motor dysfunction after stroke. In addition, whether AT and MT, either combined or alone, are more effective than the conventional treatment in the management of post-stroke upper limb dysfunction will also be determined.

**Trial registration:**

Chinese Clinical Trial Registry: ChiCTR-IOR-17011118. Registered on April 11, 2017. Version number: 01.2016.09.1.

**Electronic supplementary material:**

The online version of this article (10.1186/s13063-018-2585-8) contains supplementary material, which is available to authorized users.

## Background

Upper limb dysfunction is a common dysfunction after stroke. Of 65–80% of patients with upper limb dysfunction, 37% have varying degrees of difficulty with upper limb fine motor control [1]. Furthermore, approximately 50% are unable to complete activities of daily living (ADL) independently 3 months after stroke onset [2]. Post-stroke upper limb dysfunctions, including coordination and execution problems of the arms, palms, and fingers, cause limitations in eating, dressing, showering, and other daily activities [3], increasing the financial burden on families and society. Therefore, improving upper limb dysfunction is a significant priority for stroke rehabilitation so that patients can improve their abilities to perform ADL and optimize their quality of life.

A variety of rehabilitation treatments are available for upper limb dysfunction after stroke, including upper limb motor training, adaptive equipment or aids, and traditional Chinese medicine (TCM). However, management of upper limb dysfunction after stroke is complicated, and a single treatment is not adequate. Thus, comprehensive multidisciplinary effective measures may significantly improve the level of rehabilitation.

Currently, both acupuncture and mirror therapy (MT) are widely used for stroke rehabilitation, with MT being gradually applied by clinical researchers as a new treatment for post-stroke limb rehabilitation [4–6], particularly for severe upper limb and pain rehabilitation [7]. One study revealed that, after 1 month of MT, the functional independence measure score increased from 52 ± 17.16 to 93.18 ± 22.07, the action research arm test score increased from 15.90 ± 22.41 to 47.64 ± 15.19, and the motricity index increased from 39.27 ± 27.33 to 76 ± 21.78. Therefore, compared to conventional treatment, MT is a promising and simple method of improving motor recovery of the upper limbs of subacute stroke patients [8].

Acupuncture originated in ancient China approximately 2500 years ago as an important component of TCM. It has been used for thousands of years in several Asian countries to treat a variety of diseases. Acupuncture is simple and effective and has no adverse drug reactions. It has become a popular topic in the field of rehabilitation medicine in China. However, whether acupuncture promotes recovery from stroke remains controversial. Several studies have demonstrated that acupuncture treatment (AT) may promote the recovery of upper limb dysfunction after stroke [9–11]. One study involving a post-hoc analysis showed that the electrical stimulation group had greater improvements in hand grip (*P* = 0.015) and pinch strength (*P* = 0.007) than the control group after 4 weeks [12]. However, a systematic review showed that the methodologic quality of the included trials was inadequate and that the results may not be reliable because of substantial heterogeneity [13].

Acupuncture is a state-of-the-art TCM treatment widely utilized in China. The advantages of AT are its simplicity, convenience, affordability, and efficacy. The use of AT for the treatment of upper limb dysfunction associated with stroke is in alignment with China’s healthcare development priorities. Furthermore, MT is an important component of modern Western rehabilitation. The combination of AT and MT not only embodies the combination of Chinese and Western medicine but also reflects the integration of modern and traditional rehabilitation. If the rehabilitation program is proven to be effective, then its clinical effectiveness will be important for patients requiring rehabilitation. In addition, it is unknown whether the outcomes of combined AT and MT are superior to those of MT alone because very few studies have compared the two therapies.

Therefore, we designed a 2 × 2 factorial randomized controlled trial to explore the clinical efficacy of AT combined with MT to improve the upper limb motor function of stroke patients. We hypothesized that the synergistic effect of both therapies is greater than the sum of the individual effects of each intervention if they are used separately. AT or MT significantly improved upper limb function outcomes to a similar extent compared with the control group.

During this trial, our first aim will be to assess the synergistic effects of AT and MT on the recovery of upper limb function after stroke. Our second aim will be to determine whether AT and MT, alone or in combination, are more effective than conventional treatment for the rehabilitation of upper limb dysfunction after stroke.

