### AT combined with MT

In the combined treatment group, patients will receive AT (15 min) and MT (15 min). However, the two treatments will be performed separately, yet the order of the two treatment methods will not be limited. Each treatment will last 15 min, for a total of 30 min per session.

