### Primary outcomes

The primary outcomes in this study are the mean change in the scores on both the FMA and WMFT from baseline to 4 weeks intervention and 12 weeks follow-up between the two groups and within groups.

The FMA is widely used for motor function assessment and can reflect the functional level of stroke subjects. Even during the early stage of functional recovery, it can distinguish the level of motor function, particularly for those who have low responsiveness. The upper extremity has a maximum score of 66 points divided into three parts, namely shoulder–arm (36 points), wrist–hand (24 points), and coordination (6 points). The FMA-UE is the most common scale for evaluating upper limb motor function after stroke. It is often used as a gold standard for testing the validity of other scales as well [16, 17]. The FMA-UE has excellent reliability and validity and is sensitive enough for clinical and research practice [18].

The WMFT is the preferred scale for assessing mandatory exercise therapy for improving upper limb functions. It can either assess the quality of the patient’s completion of each activity or determine the time required for the patient to do so. The WMFT has good reliability and validity and high internal consistency [19].

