### Statistical analysis

All allocated subjects will be analyzed using the available data (i.e., on the basis of the intention-to-treat). A multiple imputation method will be used to complete missing data. Continuous variables will be expressed as mean (SD) for normal distribution or median for non-normal distribution, and categorical variables will be expressed as frequencies or percentages. A significance level of 95% (two-sided alpha *P* < 0.05) will be used.

After examining the data for normality (Kolmogorov–Smirnov test), the outcome measures will be analyzed using analysis of variance (assuming normal distribution) or Kruskal–Wallis (non-parametric). Demographic characteristics and other baseline values will be described using descriptive statistics for each group. Intragroup comparisons (changes in the FMA-UE, WMFT, VAS, SIS, and MBI scores before and after treatment) will be performed using the paired *t* test. The statistical significance of the observed differences between the groups will be assessed using 2 × 2 factorial analysis of variance to test the main effect and interaction effects of the two interventions (AT and MT). A statistician blinded to study groups will conduct statistical analysis.

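### The Background asks whether AT+MT is superior to MT alone, but neither the aims nor the stated factorial test estimates that difference, and the AT main effect cannot stand in for it

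*Protocol article*

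**What the plan says.** All places are in the protocol article.

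- **Background, rationale.** Among the reasons for the trial: "it is unknown whether the outcomes of combined AT and MT are superior to those of MT alone". The next paragraph presents the 2 × 2 factorial design as the consequence.
- **Background, hypothesis.** "the synergistic effect of both therapies is greater than the sum of the individual effects of each intervention".
- **Background, aims.** First: "our first aim will be to assess the synergistic effects of AT and MT on the recovery of upper limb function after stroke". Second: "Our second aim will be to determine whether AT and MT, alone or in combination, are more effective than conventional treatment". The comparator in the second aim is conventional treatment only. The Abstract and Discussion repeat these two targets.
- **Primary outcomes.** Changes in FMA and WMFT are to be compared at week 4 and at "12 weeks follow-up between the two groups and within groups". There are four arms, and the pair is not named.
- **Statistical analysis.** Differences between groups are assessed by a 2 × 2 analysis of variance "to test the main effect and interaction effects of the two interventions (AT and MT").
- **Treatment allocation; AT combined with MT.** Each single therapy runs 30 min a day. In the combined arm: "Each treatment will last 15 min, for a total of 30 min per session".

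**The concern.** The rationale poses a specific comparison between two arms, and the statements that follow target other quantities. A reader with the Background question in mind is likely to look for the answer in the AT main effect, because in an ordinary factorial trial that effect is the gain from adding AT whether or not MT is given.

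That reading needs two conditions, and this protocol undermines both. Effects must be additive, whereas the protocol hypothesises that they are not. The AT factor must also mean the same thing with and without MT. Here it means 30 min of AT added to conventional treatment in one half of the design, and 15 min of AT put in place of 15 min of MT in the other half.

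At stake is the interpretation of the combined arm. A significant main effect, or a significant advantage over conventional treatment, could be taken as showing a gain over MT that was never estimated.

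**Working it through.** **1. Inputs.** Sample size section: 42.86 ± 3.74 (AT) and 41.68 ± 3.44 (conventional therapy), 112 patients before attrition, 136 in total, 34 per arm, 20% attrition. Without loss n = 34 per arm. With 20% loss, 136 × 0.8 = 108.8, about 27 per arm. The planned 112 is 28 per arm. Two-sided 0.05 throughout.

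**2. The plan's own figures.** Difference = 42.86 − 41.68 = 1.18 points. Pooled SD = √((3.74² + 3.44²)/2) = 3.593. d = 1.18/3.593 = 0.328. This is AT against conventional therapy; no value is given for MT or AT+MT. The total of 112 can be matched numerically with Cohen's f = 0.3, 80% power and 2 numerator degrees of freedom (N = 111, or 112 for equal arms). Nothing below depends on that match.

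**3. What each stated test estimates.** Write C, A, M and AM for the means of the control, AT, MT and combined arms.
- AT main effect = ½[(A − C) + (AM − M)]
- Interaction = (AM − M) − (A − C)
- Question in the rationale = AM − M

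The main effect equals AM − M only if the interaction is zero.

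**4. Example.** Suppose A − C = 2.36 and AM − M = 0.
- Main effect = (2.36 + 0)/2 = 1.18. Its SE is σ/√n = 0.616 at n = 34 and 0.691 at n = 27, so the expected z is 1.91 or 1.71.
- Interaction = 0 − 2.36 = −2.36. Its SE is 2σ/√n = 1.232 or 1.383, so the expected z has the same size, 1.91 or 1.71, with the opposite sign.
- Power of each test (normal approximation) is about 48% at n = 34 and 40% at n = 27.
- The two contrasts are orthogonal, so the chance of a significant main effect without a significant interaction is about 0.48 × 0.52 = 0.25, or 0.40 × 0.60 = 0.24.

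The interaction test is therefore a partial safeguard. In about a quarter of such trials it would stay silent beside a significant main effect.

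**5. Other patterns** (simulated, 200,000 runs each; effects against control in SD units are assumptions; first figure 28 per arm, second 34).

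| AT, MT, AT+MT | AT+MT vs control | AT main effect | Positive interaction | AT+MT vs MT |
|---|---|---|---|---|
| 0.6, 0.6, 0.6 | 60%, 69% | 35%, 41% | 0%, 0% | 2.5%, 2.5% |
| 0.6, 0.6, 1.2 | 99%, 99.8% | 88%, 94% | 2.5%, 2.4% | 60%, 69% |

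In the first row combining adds nothing over MT, yet the second aim is met in most trials. In the second row the combination beats MT by 0.6 SD, but the effects are only additive, so the interaction test does not pick it up.

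**6. Precision of AM − M.** Half-width = t(0.975, 4n − 4) × √(2/n).
- n = 34: 1.978 × 0.2425 = 0.48 SD, or 0.48 × 3.593 = 1.7 points.
- n = 27: 1.983 × 0.2722 = 0.54 SD, or 1.9 points.

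If d = 0.33 is assumed for this contrast, power is 27% (n = 34) or 22% (n = 27). For both combined-versus-single contrasts to succeed at that effect it is about 13% or 10%.

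**The case against.** The opposing case is substantial.

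- **The question is background.** It is introduced as an additional point and names MT alone, not AT alone. The hypothesis and the first aim are synergy, which the interaction tests. This stands. It would be wrong to infer that the protocol sets itself the task of beating each single therapy and then forgets it; AT+MT versus AT goes beyond the stated question.
- **Synergy bears on the question.** A positive interaction means AM − M exceeds A − C, so if AT is no worse than control, the combination beats MT. This stands, but only when synergy is shown. The second aim allows a favourable conclusion on the combination without it.
- **The interaction test guards against misreading.** This is true in part, as step 4 shows.
- **Pairwise contrasts may be elsewhere.** An analysis plan not shown may list them, and the Primary outcomes wording can be read loosely as pairwise. For that reason the point is not that a contrast is absent from the article, but that the between-group test it does state does not estimate the quantity its rationale asks about.
- **No recommendation rule exists.** A reader might infer that the plan would let the combination be recommended without proof that it is better than its parts. No section states such a rule or promises such a claim.
- **The contrast is not the effect of adding AT to MT.** A reader might take it so. With 15 min of each therapy, it is the effect of replacing half the MT session with AT.

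**Conclusion.** The point holds in limited form. The Background question is not estimated by either aim or by the stated between-group test, and the AT main effect cannot be read as the gain of the combination over MT, because it averages an addition with a substitution. In the example, a true difference of 0 from MT goes with a main effect of 1.18 points, and in 24-25% of such trials the interaction test would not flag it. An advantage that is merely additive would also go undetected by the interaction test.

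The algebra follows from the design alone. The sizes assume the cited SD of 3.59, equal arms of 27 to 34, and effect patterns chosen for illustration; the protocol gives no expected value for MT or AT+MT. This is a worthwhile, inexpensive improvement. No figure in the protocol is wrong on this account.

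**What to change.** In the Statistical analysis section:

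1. Pre-specify AT+MT minus MT for FMA-UE at week 4, estimated from the factorial model already planned, with a 95% CI. Add AT+MT minus AT as a supporting contrast.
2. Describe both as comparisons at equal total session time, in which half of one therapy is replaced by the other.
3. State that no claim of an advantage over a single therapy will rest on a main effect or on the comparison with conventional treatment. Superiority over both single therapies would be claimed only if both intervals exclude zero; since both must succeed, alpha need not be split.
4. State that precision is low (step 6), so a non-significant contrast will not be read as equivalence.
5. In the Primary outcomes section, say which groups the between-group wording means.

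The cost is two contrast statements and a few sentences, with no extra patients, visits or change to treatment. The one drawback is that the low precision for this question becomes visible.

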## Methods

### Study design and setting

This trial will use a 2 × 2 factorial randomized controlled study to explore the clinical efficacy of AT combined with MT for improving the upper limb motor function of stroke patients. It will be performed in the Rehabilitation Hospitals Affiliated with Fujian University of Traditional Chinese Medicine (FJTCM). A total of 136 eligible subjects will be randomly divided into four groups, namely (1) AT group, (2) MT group, (3) combined treatment group (AT + MT), and (4) control group, in a 1:1:1:1 ratio. All subjects will receive conventional treatment, including health education and conventional medical therapy. The interventions will be performed 5 days per week for 4 weeks. AT, MT, and combined treatment (AT 15 min + MT 15 min) will be performed for 30 min per day. Therapists with more than 5 years of clinical experience will perform the interventions. A 4-week intervention and 12-week follow-up period will be conducted. Outcome measurements include the Fugl–Meyer Assessment for Upper Extremity (FMA-UE), Wolf Motor Function Test (WMFT), Visual Analogue Scale (VAS), Stroke Impact Scale (SIS), Modified Barthel Index (MBI), and adverse events. The flow diagram for this trial is presented in Fig. 1. The undertaking unit of this project (the Rehabilitation Hospitals Affiliated with FJTCM) and the ethics committees are responsible for making protocol decisions and for communicating important protocol modifications. In addition, the project undertaking unit is responsible for coordinating the work of all departments (e.g., trial registries, researcher training, informed consent of the participants, data management). If there are important protocol modifications, the project undertaking unit will notify relevant parties to convene a coordination meeting.

**Fig. 1 Fig1:**
[figure not shown]
Flow diagram of study design

### Sample size

Sample size was calculated based on the improvement in FMA-UE scores. Based on similar previous reports, the mean difference and SD were 42.86 ± 3.74 and 41.68 ± 3.44 for AT and conventional therapy, respectively [14]. We expect an effect size of at least 0.3 for outcomes after intervention. A sample size of 112 participants is required to sufficiently detect a target effect size with a type 1 error of 5% (α = 0.05) and 80% power (β = 0.20) by using Gpower 3.1.9.2 software. Considering a 20% attrition rate, a total of 136 participants are necessary, with 34 participants in each group.

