### Inclusion criteria

Eligible patients are those (1) diagnosed with stroke and confirmed by computed tomography or magnetic resonance imaging; (2) first-ever clinical stroke occurred ≤ 6 months previously; (3) FMA-UE score of ≤ 33 points; (4) modified Ashworth score of grade II or lower; (5) aged between 18 and 80 years; (6) stable vital sign and consciousness; and (7) provided written informed consent to participate.

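### The stated 80% power with 112 participants does not follow from the cited 1.18-point difference for the planned 2 × 2 tests, and the interaction, which is the first aim, has no effect size at all

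*Protocol article*

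**What the plan says.** The Sample size section opens with "Sample size was calculated based on the improvement in FMA-UE scores" and gives its source figures as follows: "the mean difference and SD were 42.86 ± 3.74 and 41.68 ± 3.44 for AT and conventional therapy, respectively". It then says "We expect an effect size of at least 0.3 for outcomes after intervention", and finally "A sample size of 112 participants is required to sufficiently detect a target effect size". Alpha is set at 0.05, power at 80%, and the software named is G*Power. After an allowance for 20% attrition, 136 are to be randomised, 34 per group. The section does not say whether 0.3 is a standardised mean difference or an analysis-of-variance effect size, nor which test was sized.

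The Background hypothesises a more-than-additive effect of the two therapies and says "our first aim will be to assess the synergistic effects of AT and MT on the recovery of upper limb function after stroke". The second aim compares each therapy, alone or combined, with conventional treatment. The Statistical analysis section tests the two main effects and their interaction by 2 × 2 factorial analysis of variance at two-sided 0.05. Under Inclusion criteria, entry requires "FMA-UE score of ≤ 33 points"; under Primary outcomes, the scale has a maximum of 66.

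**The concern.** An effect size of 0.3 sits close to the standardised difference that the cited means and SDs produce. With that difference, a two-group or main-effect comparison needs roughly 300 participants for 80% power, not 112. The paragraph's inputs and its conclusion therefore do not appear to belong together.

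The calculation also rests on acupuncture against conventional therapy, while the first aim is an interaction. For a given size of contrast, an interaction is estimated with twice the standard error of a main effect. If the stated 80% is taken at face value, a non-significant interaction could be read as evidence against synergy when the trial could have told little about it.

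**Working it through.** **Inputs.** Means 42.86 and 41.68, SDs 3.74 and 3.44, effect size 0.3, 112 evaluable (28 per cell), 136 randomised (34 per cell), 80% power: Sample size section. Two-sided 0.05 and the 2 × 2 analysis: Statistical analysis section.

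**1. Effect size implied by the cited figures.**
- Difference: 42.86 − 41.68 = 1.18.
- Pooled SD: √((3.74² + 3.44²)/2) = 3.593.
- d = 1.18/3.593 = 0.328. For a two-level factor, f = d/2 = 0.164.

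**2. Attempt to reproduce 112.** Noncentral F with four cells and noncentrality f²N, alpha 0.05, 80% power:

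| Reading of 0.3 | Numerator df | N required |
|---|---|---|
| f = 0.30 | 1 (main effect or interaction) | 90 |
| f = 0.30 | 2 | 111 (112 as a multiple of four; power 80.7%) |
| f = 0.30 | 3 (four-group test) | 126 |
| d = 0.30 (f = 0.15) | 1 | 351 |
| d = 0.328 (f = 0.164) | 1 | 294 |

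The 2-df row comes closest, but no effect in a 2 × 2 design has 2 df. One-sided two-group tests at d = 0.30 and 0.328 need 276 and 230, also far from 112.

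**3. What f = 0.30 would mean.**
- Main effect: 2 × 0.30 = 0.6 SD, or 0.6 × 3.593 = 2.2 points. That is nearly twice the cited 1.18.
- Interaction contrast: 4 × 0.30 = 1.2 SD, or 4.3 points.

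**4. Power at the cited difference.** The interaction contrast is (combined − mirror therapy) − (acupuncture − control). Its standard error with 28 per cell is SD × √(4/28), and its f is the contrast divided by 4 SD.

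| Test | Assumed size | N = 112 | N = 136 |
|---|---|---|---|
| Main effect (56 v 56; 68 v 68) | d = 0.30 to 0.328 | 35–41% | 41–48% |
| Acupuncture alone v control (28 v 28; 34 v 34), two-sample t | d = 0.30 to 0.328 | 20–23% | 23–27% |
| Interaction, contrast equal to d (assumption) | 0.30 to 0.328 SD | 12–14% | 14–16% |
| Interaction, contrast twice d (assumption) | 0.60 to 0.66 SD | 35–41% | 41–48% |

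The last row equals the first because a contrast of 2d has f = 2d/4 = d/2.

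**5. Detectable with 80% power at N = 112.** A 1-df test needs f = 0.267. That is 2 × 0.267 = 0.53 SD (1.9 points at SD 3.593) for a main effect and 4 × 0.267 = 1.07 SD (3.8 points) for the interaction contrast.

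**6. Are 42.86 and 41.68 improvements?** A mean gain of 42.86 on a 66-point scale requires a mean baseline of at most 66 − 42.86 = 23.14, with everyone then finishing at the ceiling. That is implausible as a mean change. The values may be end scores, in which case the document gives no SD of change.

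**The case against.** **The mechanism is not shown.** A reader might infer that the planners entered a standardised difference as Cohen's f. Nothing in the document states this, and another route leads to the same number. A repeated-measures group-by-time test with four groups, two measurements, an assumed correlation of 0.5 and f = 0.16 has noncentrality 0.16² × 112 × 2/(1 − 0.5) = 11.5 on 3 df, which gives 80.6% power at 112. That f is the correct conversion of the cited d. This part of the objection stands. It does not rescue the stated power, because a 3-df group-by-time test is not one of the 1-df factorial tests the protocol plans.

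**Perhaps f = 0.30 was meant in its own right.** A 1-df test would then have 88% power at 112. But the assumed main effect would be nearly twice the cited one, with no justification in the text.

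**The interaction power depends on an assumption.** This stands. A reader might take 12–14% as the trial's actual power for synergy. The document gives no interaction size, so the figure holds only if the contrast equals the cited d.

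**The SD may be the wrong one, in either direction.** This also stands. If the values are end scores with similar baseline SDs, the SD of change is SD × √(2(1 − r)), where r is the baseline–outcome correlation. It is smaller than the end-score SD when r exceeds 0.5 and larger when r is below 0.5. Baseline adjustment, which the protocol does not state, multiplies the SD by √(1 − r²). At an assumed r of 0.5, main-effect power at 112 becomes 44–51%; at 0.7, about 60–67%. Neither reaches 80%.

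**The scale argument can be pushed too far.** A reader might infer that a gain of 42 points is impossible here, or that the source patients were less impaired. Entry is at or below 33, so an individual starting at 10 could gain 56, and one entering at 33 could finish near 42. The document supports implausible as a mean change, and no more.

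**Conclusion.** The point holds. At the only difference the Sample size section cites, 112 participants do not give 80% power for either main effect or for acupuncture alone against control, and using all 136 does not close the gap. For the interaction no power claim can be checked, because no interaction size is stated. Nor does 112 match any 1-df or 3-df test in the design if 0.3 is read as f.

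The percentages rest on the cited difference and SDs, equal cells, two-sided 0.05 and no covariate adjustment; the SD of change could move them either way. The confusion of d with f remains a likely explanation, and the conclusion does not depend on it.

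**What to change.** Correct the sample-size paragraph:

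- Name the effect-size metric and the test that was sized.
- State the power at the cited difference: about 35–41% for a main effect with 112 evaluable and 41–48% with 136; 20–23% and 23–27% for a single arm against control.
- State the difference detectable with 80% power at 112: about 0.53 SD for a main effect and about 1.07 SD for the interaction contrast.
- Report the interaction as an estimate with a 95% confidence interval, so that a non-significant result is not read as absence of synergy. Synergy can remain the first aim.
- Say whether 42.86 and 41.68 are end scores or changes. If they are end scores, give the SD of change used for planning, or say that it is unknown.

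The cost is one rewritten paragraph and a less favourable stated power. No additional patients are required, and the design and planned tests stay as they are.

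### The recruitment target of 136 does not cover the stated 20% attrition: it leaves about 108 patients, not the required 112, at a cost of 1 to 2 points of power

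*Protocol article*

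**What the plan says.** The Sample size section of the protocol article builds the target in three steps.

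- Effect size: "We expect an effect size of at least 0.3 for outcomes after intervention". The metric is not given.
- Requirement before losses: "A sample size of 112 participants is required to sufficiently detect a target effect size". The stated basis is alpha 0.05 and 80% power.
- Allowance for losses: "Considering a 20% attrition rate, a total of 136 participants are necessary, with 34 participants in each group".

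The formula that leads from 112 to 136 is not shown. The total of 136 is repeated in the Abstract, in Study design and setting, and in Participants and recruitment. Under Statistical analysis, all allocated subjects are to be analysed by intention to treat, and "A multiple imputation method will be used to complete missing data". The same section plans a 2 × 2 factorial analysis of variance for the main effects and the interaction.

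**The concern.** An attrition allowance should make the number left after the expected loss at least equal to the number required. Here the requirement, the loss rate and the total are all stated in the same section, and they do not agree: 80% of 136 is less than 112. This is a conflict between stated figures, so it is not a detail that a condensed article leaves to a fuller document.

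The section is the article's only justification for the recruitment target. A reader will take it that 20% attrition is fully absorbed. If attrition does reach 20%, the number with observed outcomes falls below the declared requirement.

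**Working it through.** **Inputs.** From Sample size: 112 required, 20% attrition, 136 in total, 34 per group, effect size 0.3, alpha 0.05, power 80%. From Study design and setting: four groups, allocated equally. From Statistical analysis: two-sided alpha. Assumption: 0.3 is Cohen's f.

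**1. Reproducing 136.** 112/4 = 28 per group. 28 × 1.2 = 33.6, rounded up to 34, and 4 × 34 = 136. On the total, 112 × 1.2 = 134.4, and the next multiple of four is 136. Multiplying by 1 + 0.20 thus gives the stated figure exactly. That this was the method is an inference.

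**2. Applying the stated loss.** 136 × (1 − 0.20) = 108.8, and per group 34 × 0.80 = 27.2. In equal whole groups that is 27 each, 108 in total. The shortfall against 112 is 3.2, or 4 in whole equal groups.

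**3. The total that would keep 112.** 112/(1 − 0.20) = 140, and per group 28/0.80 = 35. Both are whole numbers, so rounding cannot explain 136. The gap is 4 patients, one per group, and 4/140 = 2.9%.

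**4. The attrition that 136 does cover.** 1 − 112/136 = 24/136 = 17.6%.

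**5. Effect on power.** Noncentral F with four groups, noncentrality N × f² and denominator df N − 4. With f = 0.3 the noncentrality is 112 × 0.09 = 10.08 at 112 and 108 × 0.09 = 9.72 at 108.

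| Numerator df | Smallest N for 80% power | Power at 112 | Power at 108 |
|---|---|---|---|
| 1 (each main effect, or the interaction) | 90 | 88.2% | 87.1% |
| 2 (not named in the article) | 111, so 112 in equal groups | 80.7% | 79.2% |
| 3 (overall four-group test) | 126 | 74.8% | 73.0% |

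The 2-df row is included only because it reproduces 112. The article mentions no such test. In the 3-df row, power is below 80% at 112, before any loss. That bears on where 112 comes from, which is a separate question.

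**6. Without relying on f = 0.3.** If the effect is set so that 112 gives exactly 80% power, 108 gives 78.5% with 1 df and 78.3% with 3 df, a loss of 1.5 to 1.7 points.

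**The case against.** Four points can be made in the plan's favour.

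- **Convention.** Adding 20% to the required number is a common habit. If the rate is read as a share of the 112, the loss is 22.4 and 136 − 22.4 = 113.6, which is enough. But an attrition rate is ordinarily the share of enrolled patients who are lost, and nothing in the section says otherwise. The wording can be defended only with a definition that it does not give.
- **Imputation.** All allocated subjects stay in the analysis, so the analysed number is nominally 136. This stands as a description of the analysis set. Imputation does not in general restore the information lost with the missing outcomes, however, and by applying an allowance the plan itself treats 112 as the number needed after losses.
- **Timing.** The primary outcomes include the assessment after 4 weeks, when total attrition may not yet have reached 20%. This stands: 108 is the number left if the full stated rate applies, not a forecast for every visit.
- **Size.** A gap of one patient per group is small beside the uncertainty in a round attrition rate and an assumed effect size. This stands too, and it limits the weight of the point.

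A reader might infer something stronger, namely that the stated 80% power is missed. The article does not support that. The dip below 80% on the 2-df reading rests on a test that is never named. On the planned 1-df factorial tests, with f = 0.3, power at 108 is still 87.1%. The 3-df figure is below 80% for reasons unrelated to attrition.

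**Conclusion.** The sample-size statement is wrong as written. On the ordinary meaning of an attrition rate, 136 patients with 20% lost leave about 108, which is 3 to 4 below the plan's own 112, and 136 covers 17.6%. This needs only the figures in the Sample size section.

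The consequence is minor: about 1 to 2 points of power on every reading tried. The power figures at f = 0.3 assume that 0.3 is Cohen's f, and whether the result lies above or below 80% depends on a test that the article leaves unnamed. That 136 came from multiplying by 1.2 is a plausible inference, not something the article states. The point calls for a corrected sentence and gives no ground to question the design or the recruitment target.

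**What to change.** Keep 136 and correct the sentence in Sample size in one of two ways:

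- say that 136 participants (34 per group) allow for about 17.6% attrition while keeping 112; or
- say that 20% attrition would leave about 108 (27 per group) rather than the required 112.

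The first is the simpler choice, because it can be written from the figures already in the section. If the second is chosen and power is restated at 108, name the test, its numerator df and the effect-size metric, since the figure cannot be checked without them.

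The cost is one sentence, and the stated allowance becomes slightly less favourable. Recruitment, allocation and analysis do not change, and the total of 136 given elsewhere in the article stays as it is.
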